### Statistical analysis

The study includes three analysis populations per analysis plan. For the baseline and efficacy data, we will use full analysis set (FAS), which includes all subjects who were randomized into the study groups and received the study operation scheme. According to the principle of intention to treat, subjects in FAS would be analyzed using their randomly assigned group, regardless of the actual surgical treatment received. Per-protocol population, e.g. a subset of FAS will be established further for subjects with no major protocol deviation(s), which will be reviewed and determined by the sponsor before the study database is locked. Safety set (SS) is defined to include all subjects who have received the treatment of the study-specified operation (regardless of whether they participate in the randomized assignment or not) and will be the primary analysis population for safety data. The subjects in SS will be grouped according to the actual surgical treatment received.

In this study, a two-sided *p*-value of 0.05 or less (equivalently one-sided p-value of 0.025) will be considered to indicate significance for any statistical tests, unless otherwise specified in the interim analysis section. Software R, V.4.0.4 [25] and SAS®, V.9.4 will be used for statistical analysis. Such data as demographics, baseline characteristics, surgery operation, radiographic data and safety will be summarized according to treatment group.

The primary endpoint of this study is the C-JOA recovery rate at 12 months post operation. It will be analyzed with the use of analysis of covariance (ANCOVA), with random stratification factors (if appropriate) and the treatment group as fixed factors, and the baseline level of C-JOA score as covariate. The least squares mean (LSM), the difference from the control group and the confidence interval (CI) of each treatment group will also provided for statistical analysis.

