For purposes indicative of statistical significance, we will use the Cochran Mantel Haenszel (CMH) method according to random stratification factors as appropriate to test the statistical hypothesis for important categorical adverse events. The incidences in each group and 95% CIs of incidence difference between the two groups will be calculated by Newcombe method [26]. Similar statistical analysis will also be conducted for each single adverse event of special interest, or Fisher’s exact test will be used for comparison between groups when applicable.

Radiographic data based on central review as their primary analyses will be compared between groups. When appropriate, we will also conduct exploratory analysis on the relationship between these imaging data and clinical outcomes, with an effort to predict the long-term clinical outcomes and complications with the use of preoperative and recent postoperative imaging data as well as other subject-level baseline characteristics. The statistical methods used for these exploratory analyses will be depicted in more details in the statistical analysis plan as appropriate.

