## Discussion

In the three recent exploratory studies [13, 14, 16], the pilot use of ACAF technique (or called vertebral body sliding osteotomy [VBSO] in principle) showed promising treatment benefits in COPLL patients. The novel surgery technique can achieve anterior direct decompression without separating and removing ossification. Its basic principle is to expand the spinal canal by anteriorly translating the involved vertebral bodies with any ossified masses [15, 16] (Fig. 2). Based on surgeons’ preference, this novel technique was initially proposed more suitable for severe COPPL patients as opposed to continue conventional anterior or posterior approaches for non-severe patients. Patients included in the small-sized studies are those with OPLL involved three or more vertebrae and a canal occupying ratio of more than 60% [13], or those with at least three levels of cervical compression caused by OPLL [14], or those with negative K-line and a large OPLL mass or kyphotic cervical alignment [16]. In line with these findings, we designed this new study to have a statistical hypothesis enriched in the severe COPLL subpopulation. To make a balanced assignment of ACAF versus LAMP across each stratum of patients and validity of subsequent statistical comparison, therefore, we pre-specified several stratification factors when conducting randomized assignment of the two treatments among enrolled subjects. This had better help set up any statistical modeling in the data analysis.

The use of anterior controllable antedisplacement and fusion belongs to one of anterior approaches, which are usually high technically demanding. However, the excellent neurologic outcome noted in the severe COPPL patients might be extended to the whole COPPL population as long as the spine surgeons in the study are rich in spine surgery experience and can also follow a standardized operation schema after uniform training held by TTC. This is why our study operation team in the sponsor’s site will design a training manual of ACAF technique, carry out field lecture and perform surgery in concert for the first several cases of each site. On the other hand, the study site is included as one of randomization factors, which provides a data basis for analyzing potential site effect in the future.

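### The safety set admits operated subjects who were never randomised and is then compared between arms, which leaves the ACAF-versus-LAMP safety comparison open to confounding of unknown size, possibly zero

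*Protocol article*

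**What the plan says.** All of the following stand in the Statistical analysis section of the protocol article.

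- **Who is in the safety set:** "all subjects who have received the treatment of the study-specified operation (regardless of whether they participate in the randomized assignment or not").
- **Its role:** it "will be the primary analysis population for safety data".
- **Its grouping:** "The subjects in SS will be grouped according to the actual surgical treatment received".
- **The contrast with efficacy:** the full analysis set is confined to "all subjects who were randomized into the study groups and received the study operation scheme".
- **What is done with safety data:** the plan uses the "Cochran Mantel Haenszel (CMH) method according to random stratification factors as appropriate to test the statistical hypothesis for important categorical adverse events". It adds that "95% CIs of incidence difference between the two groups will be calculated by Newcombe method". Each adverse event of special interest is handled similarly, or by Fisher's exact test.

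Three other sections bear on whether non-randomised subjects can exist. Study patients and Description of the interventions describe only people who are enrolled and then randomised, 164 in all. Study committees mentions demonstration surgery by the training committee. The Discussion says that the sponsor's team will "perform surgery in concert for the first several cases of each site".

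**The concern.** A safety set grouped by the operation received is usual, and that grouping is not the issue. The issue is membership. A person who was never randomised had the operation chosen, not allocated. The Background section says that surgeons and patients currently choose the approach subjectively, weighing individual benefit against complications. Choice of that kind can be linked to the risk of complications, so pooling such a person into a between-group test or interval mixes the effect of the operation with the effect of selection.

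At stake are the comparative rates of adverse events, perioperative complications and events of special interest. The monitoring board reviews adverse events at the interim analyses, and the Discussion says that the findings will feed an expert consensus and a practice guideline. A distorted difference could hide a real excess of complications or suggest one that does not exist.

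**Working it through.** **1. The plan's own figures.** The article states no figure for the safety comparison. Its only sample-size statement concerns the primary endpoint: difference 12, SD 20, two-sided 0.05, power 95%.

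- n per arm = 2 × (1.960 + 1.645)² × 20² / 12² = 72.2, so 73. The t-based solution is 73.2, so 74 per arm, or 148 in total.
- Power at 74 per arm is 95.4% (normal) or 95.2% (t).
- 148 / 0.90 = 164.4, against 164 stated.

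These figures reproduce, and the safety set does not enter them.

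**2. The two population definitions side by side.**

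| | Full analysis set | Safety set |
|---|---|---|
| Must have had the study operation | yes | yes |
| Must have been randomised | yes | no, stated expressly |
| Grouped by | assigned arm | operation received |

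In substance, the clause on randomisation is the only difference in membership. If every operated subject is randomised, the two sets hold the same people. The clause therefore matters only when a non-randomised subject exists, and then it places that person in the compared groups. The paragraph on adverse-event tests contains no exclusion.

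**3. Illustration of size.** From the article: 164 / 2 = 82 per arm, and about 12 centres (Study design). Not in the article, and assumed here: a true event risk p = 20% in randomised patients of both arms; m = 12, 24 or 36 non-randomised patients (1, 2 or 3 per centre), all in the ACAF group; and an event risk q among them of 10%, 20%, 30% or 40%.

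Bias in the incidence difference = (82p + mq) / (82 + m) − p = m(q − p) / (82 + m).

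Example: m = 36, q = 40% gives 36 × 0.20 / 118 = +6.1 points. With m = 36, q = 10% it is 36 × (−0.10) / 118 = −3.1 points.

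| m (share of ACAF group) | q = 10% | q = 20% | q = 30% | q = 40% |
|---|---|---|---|---|
| 0 (0%) | 0 | 0 | 0 | 0 |
| 12 (12.8%) | −1.3 | 0 | +1.3 | +2.6 |
| 24 (22.6%) | −2.3 | 0 | +2.3 | +4.5 |
| 36 (30.5%) | −3.1 | 0 | +3.1 | +6.1 |

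The false-positive rate of a nominal 5% two-sided pooled z test follows from the exact distribution of the two counts (ACAF: the sum of a binomial in 82 and one in m; LAMP: a binomial in 82):

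| m | q = 10% | q = 20% | q = 30% | q = 40% |
|---|---|---|---|---|
| 0 | 5.1% | 5.1% | 5.1% | 5.1% |
| 12 | 5.5% | 4.9% | 5.4% | 6.7% |
| 24 | 7.7% | 5.3% | 6.4% | 10.7% |
| 36 | 8.9% | 5.1% | 7.8% | 16.3% |

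For scale, take the cell with the largest bias, where the ACAF rate is 26.1% in 118. The simple 95% half-width of the difference is 1.96 × √(0.261 × 0.739 / 118 + 0.20 × 0.80 / 82) = 11.7 points, so the bias there is about half of it.

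**The case against.** The strongest reply is that the design has one route only: screening, enrolment, randomisation, operation. No non-randomised cohort is defined. On that design the number of such subjects is zero apart from errors, and the clause may be a safety net so that a person operated on without randomisation is not lost from reporting. This stands as a limit on size. It does not justify pooling, because a separate listing achieves the same aim.

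A reader might infer that demonstration operations and first joint cases are non-randomised ACAF patients who will fill one side of the comparison. The article does not support this. Study committees does not call the patients in demonstration operations trial subjects, and the first cases at a site could equally be randomised patients operated on jointly. If they are, they belong in the safety set.

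A reader might also infer that non-randomised patients cannot be placed in the strata of the stratified test. The factors listed under Recruitment and randomization process are site, occupation ratio, K-line status and number of vertebrae involved. All can be measured in any operated patient, so stratification is feasible. It adjusts for those factors only and does not restore random allocation.

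Finally, the article presents the safety tests as indicative, and the full analysis set and per-protocol set contain only randomised subjects. That is correct and lowers the weight of the point. The intervals for the difference will still be read as comparative evidence on safety.

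**Conclusion.** The definition is at fault as written. It expressly admits non-randomised operated subjects to the primary safety population, and the plan then compares that population between arms without excluding them. If any such subject exists and differs in risk, the comparison is biased, in either direction.

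A reader might go further and say that the safety comparison is confounded. The article does not establish that: it reports no such patients, gives no count, and leaves the status of training cases unstated. The range of −3.1 to +6.1 points rests wholly on assumed numbers and risks, apart from the 82 per arm and the 12 centres. It shows what the wording could permit, and zero is consistent with the described design. The primary endpoint, sample size, full analysis set and per-protocol set are not touched.

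**What to change.** Make three changes in the protocol and carry them into the statistical analysis plan, before adverse events are first reviewed by arm at an interim analysis:

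1. For every between-group safety test and interval, define the safety set as randomised patients who received a study operation, grouped by the operation actually received.
2. List any non-randomised operated patients separately and descriptively, outside those tests and intervals.
3. State whether demonstration operations and the first joint cases at each site involve trial subjects and, if so, whether those subjects are randomised.

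The cost is a few sentences. Any non-randomised cases no longer contribute to the comparative estimates, but their events are still reported, so no safety information is lost.

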#### Secondary outcomes

The secondary efficacy outcomes in this study included VAS pain score (range, 0 [no pain] to 10 [most severe]) [21], 10-item NDI (a total range of 0 to 50 points, the highest index the worst) [22] and 6-level Nurick disability grade (range, 0 [mild] to 5 [severe]) [23].

Safety endpoints.

The safety endpoints include any adverse events (AEs), perioperative complications, and adverse events of special interest. The AEs profile of both treatments will be evaluated by examining the incidence of AEs according to the National Cancer Institute Common Terminology Criteria for Adverse Events (NCI CTCAE, Version5.0) [24].

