### Sample size calculation

We used SAS® software, V.9.4 (SAS Institute, North Carolina, USA) to estimate sample size. According to the principle of efficacy superiority design, the significance level α was set as 0.05 at two-sided. The primary efficacy endpoint of this study is the recovery rate of C-JOA at the 12th month of follow-up post operation. Assume that in severe COPLL patient population, the mean recovery rate of C-JOA in the ACAF group and the LAMP group at 12 months after operation is 63 and 51% (a mean difference of 12%), respectively, and the common standard deviation is 20%. When the two groups are randomly assigned 148 subjects in a 1:1 ratio, the statistical power can reach as high as 95%. If the subject dropout rate is 10% or less, 164 eligible subjects with severe COPLL should be randomly enrolled.

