In addition, a mixed model repeated measures (MMRM) will be used as supportive analysis when appropriate. MMRM analysis includes treatment group, time and time treatment group interaction as fixed effects, baseline level as covariate, and patients as random effects. When there are missing data, multiple imputation method will be applied as the primary analysis; those results from the last observation carry forward method (LOCF) and the as-observed data analysis will play roles as sensitivity analyses. If the data distribution does not meet the statistical hypothesis of ANCOVA, a set of rank-based analysis will be the primary one. The LSM, the difference from the control group and the CI of each treatment group will be also provided for statistical analysis. For MMRM and ANCOVA, the two-sided *p*-values will be provided when compared with the control group.

To investigate the consistency of the trial conclusions among different subpopulations, the subgroup analysis with regards to the primary efficacy endpoint will include but not limited to the following baseline factors: gender; age group; duration of complaining symptoms; diabetes status; smoking status; count of vertebrae segments involved; type of COPLL; K-line status; occupation ratio; C-JOA score; Nurick grade and status of hypersignal of spinal cord. The occupation ratio (OR) is defined as the biggest ratio of COPLL thickness to anteroposterior diameter of the bony spinal canal on the axial computed tomography image. A forest plot will be also provided as a useful display of estimated treatment effects across subgroups.

For VAS pain score and NDI index as continuous variables, the analysis method of between-group comparison is similar to those used for the primary endpoint. For cervical Nurick grades as an ordinal variable, the common odds ratio will be estimated by using ordinal logistic regression analysis (proportional odds model) to reflect the shift of full distribution of each grade between the two groups 12 months after operation. The adjusted and unadjusted common odds ratio and its 95% CIs will be calculated. When using the model to adjust prognostic factors, the important prognostic factors mainly include random stratification factor as appropriate, gender, age and baseline Nurick score, which will be clearly specified in the statistical analysis plan before the database lock.

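### A blanket 0.05 rule lets each of the three secondary efficacy endpoints be called significant whether or not the primary endpoint succeeds

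*Protocol article*

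**What the plan says.** The threshold is written as a general rule. Under Statistical analysis, the protocol article says that a two-sided p-value of 0.05 or less "will be considered to indicate significance for any statistical tests"; the sentence exempts only what the Interim analysis section sets differently. The Interim analysis section deals only with repeated looks at efficacy and with sample size re-estimation.

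There is one primary endpoint: "The primary endpoint of this study is the C-JOA recovery rate at 12 months post operation". Under Secondary outcomes, "The secondary efficacy outcomes in this study included VAS pain score", followed by the NDI and the Nurick grade; the abstract describes these three as important. The Statistical analysis section plans a between-group comparison for each:

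- VAS and NDI are analysed in a similar way to the primary endpoint.
- Nurick is analysed by proportional odds regression at 12 months, with adjusted and unadjusted common odds ratios.

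Two further groups of analyses fall in the same section. For subgroups, "the subgroup analysis with regards to the primary efficacy endpoint will include but not limited to the following baseline factors", and twelve factors are then listed. For adverse events, important categories are tested by the CMH method, and "Similar statistical analysis will also be conducted for each single adverse event of special interest".

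Nowhere does the article rank the secondary endpoints, divide alpha among them, make them depend on the primary result, or call their p-values nominal.

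**The concern.** A missing hierarchy could be left to the analysis plan. Here, however, the protocol states a rule, and a gate or a nominal label added later in the analysis plan would depart from it. Under that rule, a trial that failed on C-JOA recovery but had p = 0.04 on VAS would report a significant benefit.

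The stated aim (Study design) is to show more favourable clinical benefits, in the plural and without tying them to the primary endpoint. The Discussion foresees an expert consensus and possibly a practice guideline built on the findings. An isolated significant secondary result could therefore carry weight that its error rate does not justify. The protocol takes care over type I error for the primary endpoint at the interim looks but applies no control to the three endpoints it calls important.

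**Working it through.** **Inputs from the protocol article**

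- Threshold: two-sided 0.05 for any test outside the interim analyses (Statistical analysis).
- Design: "the significance level α was set as 0.05 at two-sided"; means of 63% and 51%, difference 12 points, SD 20 points, 148 evaluable subjects at 1:1, power 95%, 10% dropout, 164 enrolled (Sample size calculation).
- Secondary efficacy endpoints: 3 (Secondary outcomes).
- Interim looks: two, at one-third and two-thirds of subjects, each at one-sided 0.0001; final test at one-sided 0.025 (Interim analysis).

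The correlations among VAS, NDI and Nurick are not given. I assume a common value and vary it from 0 to 0.9.

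**Step 1: the plan's own figure.** With 74 per arm, the standard error is 20 × √(2/74) = 3.288 and 12/3.288 = 3.650. Power is about Φ(3.650 − 1.960) = 0.954 (0.952 with the noncentral t distribution), so the stated 95% is reproduced. For dropout, 148/0.90 = 164.4, in line with 164 apart from rounding. This calculation uses the full 0.05 on one endpoint.

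**Step 2: the primary endpoint under the planned looks.** With information at 1/3, 2/3 and 1, the three test statistics have correlations √(1/2), √(1/3) and √(2/3). Crossing probabilities at one-sided 0.0001, 0.0001 and 0.025 give an overall one-sided error of 0.02504. The simple upper bound is 0.025 + 0.0001 + 0.0001 = 0.0252. The primary is essentially controlled for the planned looks, before any sample size re-estimation.

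**Step 3: the three secondary endpoints.** If all three null hypotheses hold and the tests are independent, the chance of at least one p ≤ 0.05 is

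1 − (1 − 0.05)³ = 1 − 0.8574 = 0.1426, or 14.3%.

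With correlated endpoints (simulation of 2,000,000 draws of three equicorrelated normal statistics, critical value 1.96):

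| Assumed correlation | Chance of at least one false significant result |
|---|---|
| 0 | 14.3% |
| 0.3 | 13.6% |
| 0.5 | 12.5% |
| 0.7 | 10.9% |
| 0.9 | 8.4% |

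Relative to 5%, this is a factor of 8.4/5 = 1.7 to 14.3/5 = 2.9. Counting only false results in favour of ACAF, the independent case is 1 − 0.975³ = 7.3%, against 2.5% for one test.

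**Step 4: with control.** A fixed sequence gated on the primary holds the familywise error across primary and secondaries at about 5%. Holm or Bonferroni within the three secondaries (first step 0.05/3 = 0.0167) would hold it at no more than 5% among those three.

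**The case against.** The best defence is that the sentence is a generic nominal threshold, that the article nowhere promises confirmatory claims from secondary endpoints, and that a hierarchy is normally found in an analysis plan, which is not shown here. This stands in part. The article does not say that a secondary result would stand as a claim after a failed primary, or that the consensus and guideline would rest on secondary p-values. It does not remove the point, because the sentence names its only exception and the secondaries are not in it.

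A reader might also infer much larger error rates by counting everything the rule touches. The document does not support that:

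- **Every test.** The interim analyses are exempted, and the primary endpoint is controlled (step 2).
- **Subgroups.** Their stated purpose is to check consistency, and the display is a forest plot of estimated effects. No subgroup or interaction test is named, so an error rate over twelve factors would describe tests that are not planned.
- **Repeated visits.** Follow-up visits are scheduled at months 3, 6, 12 and 24, but testing VAS and NDI at each is not stated. The primary analysis they follow is at month 12, Nurick is fixed at month 12, and the repeated-measures model is only supportive.
- **Adverse events.** These are tested, and the rule does reach them. Unadjusted comparison of harms is nevertheless usual, because adjustment makes harm harder to detect. The number of events of special interest is not given, and differences with 95% confidence intervals are already planned.

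**Conclusion.** The point holds for the three secondary efficacy endpoints and no further. As written, each may be declared significant at 0.05 regardless of the primary result, with a chance of at least one false declaration between 8.4% and 14.3%. That range assumes that all three null hypotheses hold, that each endpoint contributes one test at month 12, and that the common correlation lies between 0 and 0.9.

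The conclusion on the primary endpoint, its power and the sample size do not change. Severity is minor to moderate: the matter decides what may be claimed beyond the primary endpoint, not whether the trial can answer its main question.

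**What to change.** Amend the significance sentence under Statistical analysis so that the two-sided 0.05 rule applies to the primary endpoint. Then choose one of two options:

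1. **Fixed sequence.** Test NDI, VAS and Nurick at month 12 in a stated order, each at 0.05, only if the primary and every preceding secondary succeed. Name one analysis per endpoint as the one that counts; for Nurick, say whether it is the adjusted or the unadjusted model. Set the order before the first interim analysis. Fixing it only before database lock is too late in an open-label trial with two interim efficacy looks.
2. **Nominal label.** State that all non-primary p-values are nominal and support no significance claim. If the first interim analysis has already taken place (the article does not say), this is the cleaner choice.

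Under either option, keep the subgroups as estimates with 95% confidence intervals, and keep adverse-event comparisons unadjusted and descriptive.

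The cost is a wording amendment to the protocol with matching text in the analysis plan. Enrolment, data collection and primary power are unaffected. The downside of option 1 is that a later secondary cannot be claimed if the primary or an earlier secondary fails; under option 2, no secondary can be claimed as significant.

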## Methods and design

### Study design

The STAR study (ClinicalTrials.gov number, NCT04968028) is a multicentre, randomized, open-label, parallel-group, active controlled trial that aims to demonstrate more favorable clinical benefits of ACAF as compared to conventional LAMP in severe COPLL patients. It will be conducted following the Consolidated Standards of Reporting Trials (CONSORT) statement (http://www.consort-statement.org/). Approximately twelve clinical centres in China will participate in this study. A brief flowchart of this study is provided in Fig. 1.

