### Recruitment and randomization process

Before enrollment, there will be one pretreatment screening visit at study site office, during which each participant will be assigned a unique identification number.

Once considered eligible for entry, these COPLL patients will be randomly assigned to one of two study treatment groups, e.g. either ACAF or LAMP surgery in a 1:1 ratio. A stratified randomization using minimization technique [17, 18] will be carried out, stratified by study site, occupation ratio (< 60% versus ≥60%), K-line status (negative versus positive) and count of vertebrae involved (< 3 versus ≥3). Random assignment is generated by an independent statistician and implemented via central randomization mobile phone APP (Shanghai KNOWLANDS MedPharm Consulting Co., Ltd.). In order to avoid potential selection bias, the randomization sequence is concealed in APP from both clinical staff and patients until assignment. Hence, neither any investigators nor patients can influence which treatment group the study patients are assigned to.

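### The trial minimises on four factors, but the primary ANCOVA includes them only conditionally and the supportive MMRM, as specified, lists none; where they are left out, the test is conservative

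*Protocol article*

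**What the plan says.** The Recruitment and randomization process section of the protocol article states: "A stratified randomization using minimization technique [17, 18] will be carried out". The factors are study site, occupation ratio (cut at 60%), K-line status and number of vertebrae involved (cut at 3). The Study design section adds: "Approximately twelve clinical centres in China will participate in this study".

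The Statistical analysis section specifies the primary ANCOVA "with random stratification factors (if appropriate) and the treatment group as fixed factors, and the baseline level of C-JOA score as covariate". It does not say when inclusion of the factors would be appropriate.

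For the second model, the same section says that "a mixed model repeated measures (MMRM) will be used as supportive analysis when appropriate", and gives its content: "MMRM analysis includes treatment group, time and time treatment group interaction as fixed effects, baseline level as covariate, and patients as random effects". No minimisation factor is listed, even conditionally, and no residual covariance structure is named. VAS and NDI are to be compared between groups by methods similar to those for the primary endpoint.

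The Discussion says the factors were pre-specified for balance and valid comparison, and to assist later modelling.

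**The concern.** Minimisation forces the arms to be alike on its factors. If those factors predict outcome, the treatment estimate varies less from one allocation to another than it would under simple randomisation. A model that omits them does not see this: their contribution stays in the residual variance, and the standard error is larger than the true sampling variability. Confidence intervals are then too wide, the test falls below its nominal level, and precision that the design has already secured is not used.

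For the primary ANCOVA this depends on how the proviso is applied. For the MMRM it follows from the listed terms.

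The MMRM raises a second, separate question. A patient random effect with no further covariance term implies the same variance at months 3, 6, 12 and 24 and the same correlation between every pair of visits. The month-12 contrast would then be judged against a variance pooled over all four visits, not the month-12 variance.

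**Working it through.** **Inputs from the Sample size calculation section.** Recovery rate 63% against 51% (difference 12), common SD 20, 148 evaluable subjects at 1:1 (74 per arm), power 95%, 164 enrolled for 10% dropout; "the significance level α was set as 0.05 at two-sided".

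**The plan's own figure.** Normal approximation: n per arm = 2 × (1.960 + 1.645)² × 20² / 12² = 72.2, so 73. With the noncentral t distribution, power is 0.9496 at 73 per arm and 0.952 at 74, so 148 in total. Then 148 / 0.9 = 164.4, against 164 stated, a rounding difference. The figure reproduces. It uses an unadjusted two-group comparison, so nothing below changes it.

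**Step 1: omitting the factors, by formula.** Let R² be the share of outcome variance explained by the minimisation factors. Baseline C-JOA is in both models, so read R² as what remains after baseline. The documents give no value; 0.1 to 0.3 is assumed. Under perfect balance the true SE is √(1 − R²) times the reported SE. So the reported SE is inflated by 1/√(1 − R²), and type I error is 2 × [1 − Φ(1.96/√(1 − R²))].

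| R² | SE inflation | Type I error |
|---|---|---|
| 0.1 | 1.054 | 0.039 |
| 0.2 | 1.118 | 0.028 |
| 0.3 | 1.195 | 0.019 |

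**Step 2: omitting the factors, by simulated minimisation.** Balance is not perfect in practice. Assumptions: 148 patients, 12 sites (one with 25% of patients, the rest equal), three independent binary factors with prevalences 50%, 40% and 75%, biased-coin probability 0.8, total SD 20, no baseline covariate, 3,000 runs per scenario. The Monte Carlo SE is √(0.05 × 0.95 / 3000) ≈ 0.004 at a rate of 0.05.

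| R² | Type I, omitted | Type I, included | Power, omitted | Power, included |
|---|---|---|---|---|
| 0 | 0.051 | 0.050 | 0.957 | 0.950 |
| 0.1 | 0.037 | 0.048 | 0.959 | 0.965 |
| 0.2 | 0.030 | 0.051 | 0.965 | 0.976 |
| 0.3 | 0.024 | 0.047 | 0.971 | 0.990 |

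At R² = 0.2 with the factors omitted, the mean model SE is 3.29 while the estimate's actual SD is about 3.0. The power loss against adjustment is 0.6, 1.1 and 1.9 points at R² of 0.1, 0.2 and 0.3. Power with the factors omitted stays above 0.95 throughout.

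**Step 3: the MMRM's month-12 SE.** This step assumes complete data and a patient random effect as the only covariance term. The SE uses the mean of the four visit variances: √(mean variance × 2/74). The correct value at a month-12 SD of 20 is √(400 × 2/74) = 3.29. The ratio is √(mean variance)/20. Visit SDs are assumed.

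| SD at months 3/6/12/24 | Mean variance | Ratio |
|---|---|---|
| 20/20/20/20 | 400 | 1.00 |
| 16/18/20/22 | 366 | 0.96 |
| 14/17/20/22 | 342.25 | 0.92 |
| 15/17/20/20 | 328.5 | 0.91 |
| 24/22/20/20 | 465 | 1.08 |
| 26/23/20/18 | 482.25 | 1.10 |

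The distortion runs from about -9% to +10%, and is zero when visit variances are equal.

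**Step 4: cost of adjusting.** Twelve sites use 11 degrees of freedom and the three binary factors use 3, so 14 out of 148 − 2 = 146. The R² = 0 row gives the worst case: power 0.950 against 0.957.

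**The case against.** The strongest reply is that the ANCOVA sentence does name the stratification factors, and that the proviso most naturally hands details to the analysis plan. Similar wording in the Nurick paragraph comes with a promise that the adjustment factors will be fixed in that plan before database lock. The proviso also has a practical use: 148 patients over about twelve sites is roughly 12 per site, and the Discussion expects few patients at some of them. Entry requires an occupation ratio of at least 60% or at least three segments, so the cell below both cut-points should be empty.

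Much of this stands. The absence of a criterion is, taken alone, close to detail that an article may leave out. Sparse sites, however, call for a pooling rule, not an open condition on all four factors. The empty cell does no harm to a main-effects model, because three occupied cells suffice for an intercept and two effects. Unlike the Nurick paragraph, the ANCOVA sentence carries no promise to fix the factors before lock.

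On the MMRM, it is fair to say that the model is only supportive and that a patient random effect does not exclude a further residual structure. The covariance point is therefore conditional. The missing factors are not: the model's terms are listed and none of the four is among them.

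A reader might also infer more than the text supports:

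- That the primary standard error, as planned, ignores the forced balance. It does so only if the factors are dropped.
- That the plan lets the sponsor choose between two primary p-values after seeing both. The text provides for no such choice, and the unseen analysis plan may settle the matter.
- That false positives in the primary analysis rise. Omission is conservative, and the visit-variance issue cannot reach an ANCOVA that uses month-12 data only. The 15/17/20/20 pattern would give about 7.6% type I error (2 × [1 − Φ(1.96 × 0.906)]) in the supportive model alone, under one assumed set of SDs.

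**Conclusion.** The point holds as a modest one. The trial allocates by four factors, but its primary model takes them in only conditionally and its supportive model, as specified, not at all. Where they are omitted, type I error is about 0.037 to 0.024 instead of 0.05, and about 1 to 2 points of power are forgone, for R² between 0.1 and 0.3. The error is in the safe direction, and the stated 95% power survives because the trial was sized on an unadjusted SD of 20.

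The covariance point concerns only the supportive month-12 result. It requires both that the patient random effect is the sole covariance term and that variances differ by visit.

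R², the visit SDs, site sizes, factor prevalences and the minimisation probability are assumptions. Baseline C-JOA may absorb part of the factors' effect, which would move the figures towards the lower R² rows.

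**What to change.** - **Primary ANCOVA:** delete the proviso and always include occupation ratio, K-line status, vertebra count and site, alongside treatment and baseline C-JOA. Pool small sites by a rule fixed before database lock.
- **MMRM:** add the same four factors and replace the patient random effect with an unstructured within-patient covariance over months 3, 6, 12 and 24.
- **VAS and NDI:** apply the same specification.

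The cost is wording and about 14 of about 146 degrees of freedom, fewer once small sites are pooled. If the factors turn out to explain nothing, the simulated price is about 0.7 points of power. Sample size and data collection do not change.
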